## Abstract

Early implementation of interventions at a young age fosters behaviour changes and helps to adopt behaviours that promote health. Digital technologies may help to promote the hand hygiene behaviour of children. However, there is a lack of digital feedback interventions focusing on the hand hygiene behaviour of preschool children in childhood education and care settings. This study protocol aims to describe a study that evaluates the effectiveness of a gamified live feedback intervention and explores underlying behavioural theories in achieving better hand hygiene behaviour of preschool children in early childhood education and care settings. This study will be a four-arm cluster randomized controlled trial with three phases and a twelve-month follow-up by country stratification. The sample size is 106 children of which one cluster will have a minimum number of 40 children. During the baseline phase, all groups will have automated monitoring systems installed. In the intervention phase, the control group will have no screen activity. The intervention groups will have feedback displays during the handwashing activity. Intervention A will receive instructions, and intervention B and C groups will receive instructions and a reward. In the post-intervention phase, all the groups will have no screen activity except intervention C which will receive instructions from the screen but no reward. The outcome measures will be hand hygiene behaviour, self-efficacy, and intrinsic motivation. Outcome measures will be collected at baseline, intervention, and post-intervention phases and a 12-month follow-up. The data will be analysed with quantitative and qualitative methods. The findings of the planned study will provide whether this gamified live feedback intervention can be recommended to be used in educational settings to improve the hand hygiene behaviour of preschool children to promote health.

The trial is registered with ClinicalTrials.gov (registration number NCT05395988
https://clinicaltrials.gov/ct2/show/NCT05395988?term=NCT05395988&draw=2&rank=1).

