**Fig 1 pone.0280686.g001:**
[figure not shown]
Schedule of enrolment, intervention, and assessments.

This study will be a four-arm cluster randomized controlled trial study with three phases and a twelve-month follow-up by country stratification. This study will evaluate the effectiveness of the gamified live feedback intervention on children’s handwashing behaviour, self-efficacy, and motivation in three different phases: the baseline, intervention, and post-intervention phases. In Finland, there will be a twelve-month follow-up after the baseline phase. This study will consist of four groups, the control group, and three different intervention groups. All the groups will have automated monitoring systems installed before the start of the baseline phase and will be available in all phases. The system will be de-installed after the post-intervention phase.

During the baseline phase, all the groups will have no screen activity. During the intervention phase, the control group will have no screen activity. The intervention A group will have a screen display providing handwashing instructions but no reward, and the intervention B and C groups will receive handwashing instructions and rewards from the screen display. During the post-intervention phase, all the groups will have no screen activity except the intervention C group which will receive handwashing instructions but no reward (Fig 2).

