### Implementation

This study will be composed of three phases, the baseline, intervention, post-intervention, and a twelve-month follow-up (Fig 2). The first phase will be the baseline which will last for three weeks. The systems will be installed in the kindergarten sinks which will collect data from the handwashing activities, but it will not provide any feedback or screen activity. A “how-to” teaching session (video-based training) will be held in each kindergarten in the middle of the baseline phase for all children to learn the same hand hygiene information. The second phase will be the treatment and will last for three weeks. The third phase will be the post-intervention, and it will also last for three weeks. After this phase, the systems will be de-installed from all the kindergarten sinks. In Finland, there will be a twelve-month follow-up after the intervention.

The control group will have no screen display next to the sink throughout the study. The intervention A (instruction) group will receive instructions from the screen display next to each sink where handwashing instructions are shown during the handwashing activity but no reward after. The intervention B (reward) and intervention C (reward plus instruction) groups will receive instructions and rewards shown on a screen display right next to the sink during the intervention phase. In these groups, handwashing instruction is shown during the handwashing activity and if handwashing is done correctly (based on time and soap usage), a reward of animal animation is shown on the screen, see Figs 6 and 7. During the post-intervention phase, the intervention C group will remain to have the screen display receiving instructions with no reward. In Finland, sick leave days of the children and kindergarten staff will be tracked (Fig 8).

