### Data analyses

Data will be analysed using qualitative and statistical methods. All eligible participants will be included in the analysis. The statistical analyses will be performed with R. The categorical and numerical data will be analysed using one-way analysis of variance (ANOVA). Qualitative analysis will be presented thematically [42].

For the measurement data from the system:

Data pre-processing: Data will be investigated where water and soaping data are combined to single handwashing procedures. Data points that are not valid (outside of kindergarten opening hours) will be removed. The descriptive statistics of the clusters, randomization checks, ICC (intracluster correlation) will be calculated. The data will be analyzed using linear fixed-effect regression model for panel data, and dependent variable soaping time. The four groups will be compared in baseline, intervention, and post-intervention phases.

For the survey and staff interview data:

The comparison among the groups will be implemented using random effects regression, allowing for the clustered nature of the data, and adjusted using the covariates of the adjusted analyses (when a small number of clusters are present) [43]. Simple bias analysis will be used to quantify the uncertainty of the biases such as confounding variables [33]. The qualitative results of the survey and kindergarten staff interview will be analysed and compared thematically. The four groups will be compared after intervention phase.

For the children interview and observation data:

The analyses will be compared among groups based on the complete data only. The comparative analyses approach used to calculate the observation, survey, and staff interview will be used. The self-efficacy measurement scale will be developed and evaluated for its psychometric properties [44,45]. The qualitative result of the observation and interviews will be analysed and compared thematically [42]. Children who will participate the interview at one time point will be considered as missing data, these will be excluded from the analysis. The four groups will be compared in baseline, intervention, and post-intervention phases.

For the sickness day data:

The total sick leave days are compared among the groups one year before and after the start of the baseline phase.

The statisticians of the two universities will validate the statistical results of the data.

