This study will use multiple measurements such as a monitoring system, survey, interview, and observation to assess hand hygiene behaviour, self-efficacy, and motivation. This will provide versatile data to support the effectiveness of the intervention. It will also provide information if self-efficacy and motivation play important roles in attaining hand hygiene behaviour. Another is to provide further evidence if preschool children’s self-efficacy is a significant variable in determining the effectiveness of the intervention and obtaining hand hygiene behaviour. In this study, hand hygiene self-efficacy for preschool children will be developed and evaluated which up to these days none have been developed. This study will also measure the sick leave days of the children and kindergarten staff which could give information if using the intervention is effective in reducing the number of sick leave days. Hand hygiene interventions in educational settings showed to decrease the spread of infectious illnesses [3,7] and reduce absenteeism [3]. This study will use a cluster randomized controlled design which includes larger participants and a long follow-up period. Systems will be installed in all the groups which can provide concrete data on the handwashing activities. Another strength of this study will be assessing the children’s self-reports as there are few interventional studies that measured this. Evaluating the effectiveness of the gamified live feedback intervention will enable the research team to determine if this kind of approach is worth implementing to improve handwashing practices in various settings i.e., clinical, and educational settings.

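### The abstract promises handwashing, self-efficacy and motivation data at 12 months, but the methods text schedules only Finnish sick-leave days beyond week 9

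*Protocol article*

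**What the plan says.** The Abstract lists the outcomes: "The outcome measures will be hand hygiene behaviour, self-efficacy, and intrinsic motivation". The next sentence gives their timing: "Outcome measures will be collected at baseline, intervention, and post-intervention phases and a 12-month follow-up". It neither mentions sick leave nor limits the follow-up to one country. The Limitations section returns to the idea. Having noted that Covid-19 may affect how children wash their hands, it offers as a response the comparison of four groups at three time points and at 12 months.

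The Trial design section says of the sensors: "The system will be de-installed after the post-intervention phase". The Implementation section repeats this and gives each of the three phases three weeks, beginning with: "The first phase will be the baseline which will last for three weeks".

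The follow-up itself is dated twice. Trial design has: "In Finland, there will be a twelve-month follow-up after the baseline phase". Implementation has: "In Finland, there will be a twelve-month follow-up after the intervention".

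For sick leave, which the Outcome measures section makes tertiary and restricts to Finland, Data analyses states: "The total sick leave days are compared among the groups one year before and after the start of the baseline phase". Data collection uses the same window. The Discussion describes the design as one "which includes larger participants and a long follow-up period".

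**The concern.** A reader of the abstract would expect the primary outcome and both psychological outcomes to be measured a year on, in both countries. Whether the effect lasts is central to this trial: the hypotheses ask whether a habit forms, whether behaviour falls back to baseline, or whether reward crowds out motivation. If nothing behavioural is measured after week 9, the trial can speak to these questions only over the three-week post-intervention phase, and the abstract credits it with a property that the methods do not give it.

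Two smaller matters follow from the same text. The 12-month period has no single start date. And the one variable that does cover a year is to be compared as a total number of days, which depends on how many children and staff are enrolled as well as on how often they are ill.

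**Working it through.** **Step 1: when data collection ends.** Inputs: three phases of three weeks each (Implementation), taken as running back to back.

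3 + 3 + 3 = 9 weeks from the start of baseline to removal of the sensors.

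**Step 2: what is scheduled, source by source** (Data collection and Data analyses, with the outcome definitions in Outcome measures).

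| Source | Outcome served | Last scheduled collection |
|---|---|---|
| Faucet and soap sensors | Handwashing (primary) | Post-intervention phase, by week 9 |
| Child interviews | Self-efficacy, motivation | Last week of post-intervention |
| Observation sessions | Handwashing in kindergarten | Last week of post-intervention |
| Parent survey | Handwashing at home | Last week of intervention |
| Staff interviews | Handwashing in kindergarten | First week of post-intervention |
| Sick-leave records (Finland) | Tertiary | One year after the start of baseline |

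The planned comparisons match this schedule: the three phases for sensor, interview and observation data, and after the intervention for the survey and staff data. None is at 12 months except sick leave. The Data collection paragraph on follow-up strategy describes emails, reminders and contact details; it does not name an assessment.

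**Step 3: when the 12 months begin.** Week 0 is the start of baseline, and a year is taken as 52 weeks.

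| Where | Start | End (start + 52) | Weeks shared with weeks 0–52 |
|---|---|---|---|
| Data collection, Data analyses (sick leave) | 0 | 52 | 52 |
| Trial design (follow-up) | 3 | 55 | 49 (49/52 = 94%) |
| Implementation (follow-up) | 6 | 58 | 46 (46/52 = 88%) |
| Implementation, if it means after the last phase | 9 | 61 | 43 (43/52 = 83%) |

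The start points differ by 3 to 6 weeks (3/52 = 5.8%; 6/52 = 11.5%), or by up to 9 weeks on the last reading. With the week 0 start, the first 3 of 52 weeks (5.8%) come before any display is switched on.

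**Step 4: totals against rates.** Let a kindergarten have N enrolled children and r sick days per child-year, so that its total is N × r.

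- With stable enrolment and no effect, the before-to-after change is N × r − N × r = 0 and the ratio is 1, whatever N is.
- If the intervention lowers the rate by d days per child, the total falls by N × d. For illustration, take the pre-study group sizes of 82 and 53 from the Sample size section and assume d = 1. The totals fall by 82 and 53 days, a factor of 82/53 = 1.55 for the same effect per child.
- If enrolment changes between the years at a constant rate, the total shifts by r for each net child gained or lost. At assumed rates of 5, 10 or 15 days per child-year, that is 5, 10 or 15 days. In a kindergarten of the planned size of 40, one net child moves the total by 1/40 = 2.5% with no effect at all.

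**The case against.** **The figures might hold a 12-month assessment.** Data collection refers the timeline to Figs 1 and 2, which are not reproduced in the text reviewed. This stands as a caveat for interviews and surveys. It cannot rescue the primary outcome, because sensors that have been removed record nothing, and the written schedule gives explicit times without a 12-month visit.

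**No hypothesis needs 12-month behaviour.** This is correct. The hypotheses are framed within or just after the study phases, so no planned test fails. The fault lies in what the abstract and limitations say the trial will measure.

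**The long follow-up in the Discussion may mean sick leave.** This is fair: the phrase comes straight after sentences on absence and illness. It does not say so, however, and beside the abstract it invites a reading about behaviour.

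**Sick leave does not have three start points.** A reader might infer that it does. The documents do not support that: both sections that date the sick-leave window use the start of baseline. The clash is with the general follow-up in Trial design and Implementation. The shift is also modest, and the three untreated weeks fall in every arm alike, so they dilute slightly and do not by themselves bias the arms against each other.

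**Totals do not automatically favour the smaller kindergarten.** A reader might infer that two kindergartens of different size would show a spurious effect in proportion to their size. That follows only if the prior year is ignored, and the plan compares before with after. With stable enrolment and no effect, the change is zero at any size, as Step 4 shows.

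**The sick-leave model is detail for an analysis plan.** This stands in part: a condensed article need not give the model, and it does not exclude a rate. But it does name the total as the quantity to be compared, and that choice can be improved.

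**Conclusion.** The contradiction holds. The abstract, echoed in the limitations, claims 12-month collection of handwashing, self-efficacy and motivation. The methods remove the sensors after week 9 and schedule no such data later. What the text does support is three weeks of observation after the displays change, plus one year of sick-leave days as a tertiary outcome in Finland. For the German kindergartens it supports no 12-month data at all. This should be corrected, because it changes what the trial can conclude about lasting behaviour.

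The inconsistent dating of the follow-up is secondary: 3 to 6 weeks, or up to 9. The use of totals is the weakest part. It is a matter of scaling and of enrolment turnover, not a built-in bias towards one arm.

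The conclusion assumes that the phases are consecutive and that the missing figures add no 12-month interview or survey. The statement about the sensors does not depend on the figures.

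**What to change.** - **Abstract and Limitations:** state that handwashing, self-efficacy and motivation are followed to the end of the three-week post-intervention phase, and that the 12-month follow-up is sick leave in Finland only.
- **Discussion:** say that the long follow-up refers to sick leave, not to behaviour.
- **Trial design, Implementation, Data collection and Data analyses:** use one start date for the 12-month period.
- **Sick-leave analysis:** replace total days with days per enrolled child-day and, separately, per enrolled staff-day, each compared with the same kindergarten's rate in the prior year.
- **Figs 1 and 2:** check that they agree with the corrected text.

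Most of this is wording. The rate needs enrolment and staffing counts for both years from the kindergartens. The other cost is that the stated follow-up becomes less favourable.

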## Introduction

Children’s development is motivated by their efforts to understand the unknown. They learn by experimenting and doing, it is when curiosity is stimulated, that children gain knowledge [1]. From birth to 12 years old, children are active, eager to connect, and motivated social learners, making this development stage ideal for enhancing essential attitudes and behaviours [2].

Educational settings are important places to instil healthful behaviours in children and they offer environments that impact children’s behaviour [3]. Early implementation of interventions at a young age fosters behaviour change and helps to adopt behaviours that promote health [4]. It is known that children’s behaviour can be carried out to adulthood [1,2]. The guidance supports the development of their learning abilities, thinking, habits, and behaviours, and find their independence.

Highly infectious illnesses rapidly spread in semi-close places such as in educational settings [5]. Children cared for in day-care and preschool education have higher risks of acquiring infections than those cared for at home [6]. Children’s bodies are vulnerable which make them susceptible to infections [5]. The common infectious illnesses of children are respiratory and gastrointestinal [3,5]. Illnesses that can be prevented through hand hygiene.

Hand hygiene is the most cost-effective method and fundamental behaviour to prevent the spread of infections in educational settings [5,7]. It also reduces infectious illnesses-related absences among children [7]. The commonly used method for hand hygiene promotion is through health education but promoting better hand hygiene practices is more effective [3]. Limited data are available on monitoring hand hygiene practices among children in educational settings and it is challenging because it demands time and resources.

Hand hygiene interventions are any form of techniques to be performed to promote hand hygiene behaviour [5,8]. Hand hygiene interventions that could enhance psychosocial variables such as behavioural capacity, attitudes, and subjective norms are widely used in educational settings [3,9]. Also, incorporating behaviour change techniques and play in hand hygiene interventions for children provide effective results in promoting hand hygiene behaviour [10,11] and building self-efficacy in handwashing [12,13]. Many of these studies that used hand hygiene interventions among children in educational settings evaluated effectiveness in reducing infectious related-absenteeism [5,11,14], decreasing infections [5,7], hand hygiene compliance [4,15,16] and microbiological effect [14].

Determining the mediating variables of health behaviours create a foundation for the success of the health behavioural change interventions [9,17]. One of these variables is self-efficacy, a belief in one’s capabilities to accomplish a certain task and could account for the effect of an intervention [18]. It is regarded that self-efficacy is one of the variables that influence the adoption and maintenance of health behaviour [12,19]. Motivation also plays a significant role in learning and behaviour changes [8,12]. Children with a higher sense of self-efficacy tend to have better motivation [12,20].

The use of gamification as interventions have been growing due to their enjoyable elements [21]. Gamification is the use of gamified elements in non-gaming settings [22]. Studies showed that users of gamified interventions appeared to have increased motivation to perform tasks and maintain healthy behaviours [21,23,24]. Enhancing children’s experiences with positive and enjoyable approaches can support them grow into healthy adults [25].

Young children’s experiences with technology are becoming part of the daily context of their lives(26). Appropriate frameworks for the use of technology and interactive media are tools that can help to promote effective learning and development [26,27]. Novel digital technologies adopted in the educational environment may help to promote sustainable handwashing behaviour of children across various settings [28]. However, current digital health technologies have been developed mainly for clinical settings [29]. This study will investigate the effect of gamified digital intervention with live feedback on preschool children aged three to six years old in early childhood education and care settings using a cluster randomized controlled trial.

## Methods

### Aim of the study

This article introduces the protocol for the Candy study: Improving children’s hand hygiene which aims to evaluate the effectiveness of a gamified live feedback intervention and explore underlying behavioural theories in achieving better hand hygiene behaviour of preschool children aged three to six years old in early childhood education and care setting to promote health.

### Objective and Hypotheses

This study will evaluate the effect of the gamified live feedback intervention on promoting hand hygiene behaviour and increasing self-efficacy levels of preschool children, and if motivation crowding-out will happen. Crowding out is an effect where there is a decrease or lack of motivation to perform handwashing because the reward is already known or expected [30].

### Hypotheses

Main effects: Control, Intervention A (instruction), Intervention B (instruction plus reward), and Intervention C (instruction plus reward and instruction in post-intervention phase) groups

H1: Feedback display will increase handwashing activity in the kindergarten (in the short term) during intervention phase
For intervention A, B, and C groupsFor intervention B and C groups more than intervention A groupH2: Handwashing activity in the kindergartens will decline with time (while the display will still be turned on)
For intervention A group less than intervention B and C groups during the beginning of the post-intervention phaseFor intervention B group less than intervention C group during post-intervention phase.For control group less than intervention A, B, and C groups in all phases.Motivation crowding out: Measurement-basedH3a: Effect will partially persist, when feedback display in kindergarten will be turned off during the beginning of post-intervention phase. For intervention C groups less than intervention A and B groups. (Explanation: habit will be formed, there will be partial motivation crowding out, impact in increased self-efficacy will be stronger)H3b: Effect will vanish and handwashing will return to baseline behaviour for intervention B group in post-intervention phase. (Possible explanation: no habit will be formed, there will be no motivation crowding out)H3c: Effect will vanish and handwashing activity will drop below baseline behaviour for intervention A group in post-intervention phase. (Possible explanation: there will be crowding out)
Acquisition of competences and self-efficacy: Intervention A, B, and C groupsH4a: Feedback intervention will increase competences and self-efficacy level of children after the intervention phase–for intervention B and C groups stronger than for intervention A groupH4b: Feedback intervention will increase competences and self-efficacy level of children after post-intervention phase–for intervention C group stronger than for intervention B group and for intervention B group stronger than for intervention A group.

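### H3b predicts a return to baseline in arm B, but the plan lists only tests for a difference, so that part of H3b can be refuted but not supported

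*Protocol article*

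**What the plan says.** The objective in the Protocol article includes finding out whether motivation crowding-out occurs. Under Hypotheses, three measurement-based statements address it, each tied to particular arms:

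- H3a expects partial persistence early in the post-intervention phase and compares arm C with arms A and B.
- H3b concerns arm B: "H3b: Effect will vanish and handwashing will return to baseline behaviour for intervention B group in post-intervention phase". The text adds, in brackets: "Possible explanation: no habit will be formed, there will be no motivation crowding out".
- H3c concerns arm A: "H3c: Effect will vanish and handwashing activity will drop below baseline behaviour for intervention A group in post-intervention phase".

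No figure says how close to baseline counts as a return.

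Under Data analyses, one-way ANOVA is named in general. For the faucet data the plan says: "The data will be analyzed using linear fixed-effect regression model for panel data, and dependent variable soaping time". It adds: "The four groups will be compared in baseline, intervention, and post-intervention phases".

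Under Sample size, the calculation uses a large effect (f² = 0.35), power 0.8, level 0.05 and two predictors, then a design effect from an ICC of 0.062 and 40 children per kindergarten. It arrives at 106 children in three kindergartens.

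**The concern.** A test for a difference can show that arm B has not returned to baseline. It cannot show that arm B has. H3a's persistence and H3c's fall below baseline can each be supported by a significant result in the arms they concern. For the baseline-return part of H3b, the only result in its favour under the listed methods is a non-significant one, and a non-significant result also arises when the estimate is merely imprecise.

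This matters because the protocol attaches a behavioural reading to H3b: no habit and no crowding-out. If the contrast is imprecise, a sizeable remaining effect, or a real fall below baseline, could sit behind a result that looks like a return. Crowding-out is part of the stated objective, so this conclusion is likely to be reported.

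**Working it through.** **1. The plan's own sample size.** For an overall F test with f² = 0.35, two predictors and level 0.05 (noncentrality 0.35·N, degrees of freedom 2 and N − 3), power is 0.7885 at N = 30 and 0.8041 at N = 31. So n = 31 reproduces. The design effect is 1 + 39 × 0.062 = 3.418, and 31 × 3.418 = 105.96, which gives 106. (The multiplier printed in the product, 4.418, would give 136.96, so it is a misprint; the total of 106 is consistent with 3.418.) The figure of 106 comes from detecting a large effect, not from bounding a small one.

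**2. Inputs for the H3b contrast.**
- ICC 0.062 (Sample size section).
- One kindergarten in arm B. This is an assumption, and a favourable one: the plan needs three kindergartens for four arms and has one cluster cover two intervention groups.
- Correlation ρ of the kindergarten effect between baseline and post-intervention phases. The document does not give it, so 0, 0.5 and 0.8 are assumed.
- Total SD set to 1, since no SD of soaping time is given.
- Sampling error within the kindergarten is ignored, which again favours the plan.

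**3. Standard error of arm B's post-minus-baseline difference.** SE = √(2 × 0.062 × (1 − ρ)).

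**4. Chance that a true departure d is non-significant (two-sided 5%).** Φ(1.96 − d/SE) − Φ(−1.96 − d/SE), with d = 0.5 SD:

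| ρ (assumed) | SE (SD units) | d/SE | Non-significant |
|---|---|---|---|
| 0 | 0.352 | 1.42 | 71% |
| 0.5 | 0.249 | 2.01 | 48% |
| 0.8 | 0.157 | 3.18 | 11% |

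For d = 0.2 SD the same formula gives 91%, 87% and 75%. For d = 0.8 SD it gives 38%, 11% and 0.1%.

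**5. What an interval could show.** The half-width of a 90% interval is 1.645 × SE: 0.58, 0.41 and 0.26 SD at the three correlations. A margin narrower than the half-width could never be met, even if the estimate were exactly zero.

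**The case against.** Several objections have force.

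- A reader might infer that the investigators will treat p > 0.05 as proof that the effect vanished and nothing was crowded out. The document does not say so. It states no decision rule, and it calls the absence of habit and of crowding-out a possible explanation, not a conclusion.
- A reader might also treat H3a, H3b and H3c as three rival verdicts on one estimate, with an imprecise result falling to H3b by default. The Hypotheses section does not support this: H3b belongs to arm B, H3c to arm A, and H3a compares arm C with A and B. A null result in arm A fails to support H3c; it does not support H3b.
- Part of H3b can be tested in the ordinary way. A vanishing effect implies a fall from the intervention to the post-intervention phase, and the plan compares all three phases. Only the return to baseline is affected.
- A margin may stand in an analysis plan that is not shown. Its absence from an article is not in itself a fault. What remains is the mismatch in print: a no-difference prediction beside methods that look for differences and a sample size based on a large effect.
- The size depends on an undocumented correlation. At 0.8, non-significance is fairly informative about a 0.5 SD departure. Miss rates that count children as units would look worse, but they do not fit faucet data, which carry no person identifiers.
- The error could run the other way. If every handwash were treated as independent, with about 1,250 per arm and phase (10,000 pre-study events × 21/42 days ÷ 4 arms, assumed), a difference of 1.96 × √(2/1250) = 0.08 SD would be significant and a nearly complete return would be rejected. The document does not settle which error would occur. Neither case makes the difference test a measure of return.

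**Conclusion.** The point holds for the baseline-return part of H3b. As printed, that part can be refuted but not supported, and a non-significant contrast would be weak evidence of return, of no habit or of no crowding-out. A true 0.5 SD departure would go undetected about 71%, 48% or 11% of the time at assumed between-phase correlations of 0, 0.5 or 0.8. These figures rest on the plan's ICC, one kindergarten in arm B and no sampling error within it, so actual precision is likely to be worse. H3b does not drive the sample size and is one of several mechanism hypotheses. It bears on a stated objective, though, so the change should be made.

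**What to change.** Keep the regression and change how H3b is judged:

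- Report arm B's post-intervention minus baseline difference in soaping time with a confidence interval that allows for clustering. Three kindergartens cannot estimate the between-kindergarten variance, so an external value such as the pre-study ICC would have to be used and stated, along with the assumed between-phase correlation.
- State that a non-significant difference will not be read as a return to baseline, or as absence of habit or of crowding-out.
- Claim a return only if the whole interval lies inside a margin on soaping time that the investigators fix and justify before seeing the data. Otherwise report H3b as inconclusive.
- Leave H3a and H3c with the arms to which the Hypotheses section assigns them.

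The margin needs a behavioural justification. A fixed share of the planning effect is not a safe default: in a two-group contrast f² = 0.35 corresponds to 2 × √0.35 = 1.18 SD, and half of that, 0.59 SD, would accept the 0.5 SD departure examined above.

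The cost is a few sentences, the work of justifying the margin, and no new data. Given the half-widths above, H3b may well be reported as inconclusive.
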